## Abstract

Background

As desmoid-type fibromatosis (DF) exhibits a high recurrence rate after surgery, initial active surveillance followed by medical therapy is the mainstay of the treatment. However, there are few effective drugs with acceptable side effects.

Methodology

Among drugs that have been used for a long period and possess a known safety profile, auranofin was observed to be effective in suppressing DF using the drug repositioning method in our laboratory. This clinical study has been designed to examine the efficacy and safety of auranofin, an approved anti-rheumatic drug, in patients with progressive DF.

Results

This study is conducted as a single-center, single-arm, open-label study. Auranofin 3 mg tablets will be administered twice daily to DF patients with progressive disease. The primary endpoint is progression-free survival at 26 weeks after starting treatment. Secondary endpoints include response rate, T2-weighted MRI evaluation, pain intensity, quality of life (QOL), and safety assessment.

Conclusions

This is the first clinical trial of auranofin in patients with aggressive DF. The study will allow an in-depth understanding of the efficacy of auranofin for response rate as well as for changes in MRI findings, pain, and QOL in patients with aggressive DF.

## Introduction

Desmoid-type fibromatosis (DF) is a (myo-)fibroblast-proliferating soft tissue tumor that is classified as an intermediate locally aggressive tumor in the new 2020 WHO classification [1]. DF is a rare disease that occurs in 2.4-4.3 people per million individuals per year, and the site of occurrence is generally divided into intraperitoneal and extraperitoneal tumors. The majority of extraperitoneal tumors are thought to be caused by mutations in the *β-catenin* gene and commonly affect the abdominal wall, shoulder girdle, buttocks, and extremities [2]. DF that occurs in familial adenomatous polyposis patients often arises in mesenteric or retroperitoneal regions and possesses an adenomatous polyposis coli germline mutation [3].

Among bone and soft tissue tumors classified as intermediate types, DF is characterized by a significantly high postoperative recurrence rate and spontaneous regression in some cases. Additionally, in numerous cases, activities of daily living (ADLs) and quality of life (QOL) may worsen due to joint contracture and pain caused by DF during follow-up and after surgery [4]. Based on these findings, the standard treatment for DF is surgical treatment aiming for an R0 resection; however, the mainstay of treatment becomes active surveillance involving careful follow-up without any active therapeutic intervention. Experts from Europe, America, and Asia have published a statement of treatment policy for DF based on past literature reviews [5]. In this manuscript, the first option in the treatment algorithm for DF is active surveillance. However, there are a significant number of cases in which DF cannot be controlled with active surveillance. In such cases, implementation of active treatment is necessary to control the disease [6,7]. Specifically, there are cases in which a drug with evidence of effectiveness is required.

Drugs that have long been used to treat DF include non-steroidal anti-inflammatory drugs (NSAIDs), antihormonal drugs, anticancer drugs, and molecular target drugs [8]. Among these, certain anticancer drugs and molecular target drugs have been reported to be effective [5]. Combination therapy involving the use of methotrexate (MTX) and vinblastine (VBL) has long been used as an anticancer therapy. Azzarelli et al. administered MTX 30 mg/m^2^ + VBL 6 mg/m^2^ once each week to 30 DF patients and observed that partial response was achieved in 12 (40%) patients and stable disease in 18 patients. Conversely, serious bone marrow suppression was reportedly observed in four (13%) patients as an adverse event [9]. The results of combined therapy of MTX and VBL have been reported for 38 cases of DF in Japan, and the clinical benefit rate was 95%. Progression-free survival (PFS) at five years was 80.8%. However, three cases of grade 3/4 adverse events were observed [10]. The effectiveness of doxorubicin-based chemotherapy has also been reported. However, considering that DF is not a malignant tumor, many facilities use doxorubicin treatment which is known to elicit strong side effects as a third-line drug treatment [8].

Several molecular-targeted drugs have also been demonstrated to be effective against DF. Gounder et al. conducted a double-blind randomized controlled trial reporting the efficacy of sorafenib for progressive DF [11]. The median follow-up period in this trial was 27 months, and the two-year PFS rate was 81% in the sorafenib group and 36% in the placebo group. These rates were statistically significant, thus demonstrating the efficacy of sorafenib (p < 0.001). In the sorafenib group, the response rate was 33%, and the median time to tumor shrinkage and evaluation was 9.6 months. Toulmonde et al. reported the results of a multicenter, phase II, randomized, open-label study of pazopanib versus MTX + VBL for progressive DF (DESMOPAZ study) [12]. In this study, a one-year PFS rate of 85.6% was reported in the pazopanib group. The main side effects of pazopanib were hypertension and diarrhea. Recently, the effectiveness of nirogacestat in progressive DF has been reported [13]. However, these molecular-targeted drugs are expensive and cause significant side effects.

Considering the current state of drug treatment for DF, a study was conducted using drug repositioning techniques to discover new drugs that elicit few side effects and are relatively inexpensive. Using Prestwick’s Chemical Library which contains 1,186 off-patent pharmaceutical products that comprehensively cover a wide range of disease areas, we screened drugs that are effective against DF in an in vitro experimental system using several DF cell lines. The antirheumatic drug auranofin was identified as exerting anti-DF tumor effects. The antitumor effect of this drug was also observed in vivo using a mouse model of spontaneous DF onset [14].

Auranofin has long been used to treat rheumatoid arthritis and possesses a proven safety profile for long-term use. As it is inexpensive and causes few side effects, we decided to plan the first clinical trial of auranofin in patients with progressive DF.

## Materials and methods

Study design

The study design will be a single-center, single-arm, open-label exploratory study. This clinical study will be conducted at one facility, the Nagoya University Hospital.

Study objective

This study will be the first clinical trial to examine the efficacy and safety of auranofin, an antirheumatic drug already approved, in patients with DF (Figure 1).

**Figure 1 FIG1:**
[figure not shown]
Flowchart of the study procedure.

Endpoints

The primary endpoint will be PFS at 26 weeks after the start of treatment. The secondary endpoints will be the following: (i) to (vi) at 12 and 52 weeks after the start of treatment; (i) to (v) at 26 weeks; the best response during the study period (Table 1). Throughout the study period, safety will be assessed according to the Common Terminology Criteria for Adverse Events, version 5.0.

**Table 1 TAB1:** Study endpoints.

Endpoints
(i) Response rate (MRI or CT according to the Response Evaluation Criteria in Solid Tumors (RECIST ver. 1.1): CR (complete response)/PR (partial response)/SD (stable disease) rate
(ii) Percentage of high-intensity areas in T2-weighted MRI
(iii) Pain scale assessment using the Numerical Rating Scale (NRS)
(iv) Quality of life (QOL) assessment using the EuroQol 5-dimensional questionnaire (EQ-5D)
(v) GODDESS (Gounder/DTRF Desmoid symptom/Impact Scale [15], NIH-Developed QOL Assessment for DF)
(vi) Progression-free survival

Eligibility criteria

Inclusion and Exclusion Criteria

Patients who meet all of the conditions listed in Table 2 will be selected, and those who meet one of the conditions listed in Table 3 will be excluded.

**Table 2 TAB2:** Inclusion criteria.

Inclusion criteria
(i) Patients who have been definitively diagnosed with desmoid-type fibromatosis (DF) by the time of consent. Both the sporadic type and the familial adenomatous polyposis type are acceptable
(ii) Patients aged 18 years or older at the time of consent
(iii) Patients with evaluable lesions
(iv) Patients with tumor progression within six months prior to the start of the clinical study or patients with inoperable disease and worsening functional disability
(v) Patients who have provided written informed consent
(vi) Patients with Eastern Cooperative Oncology Group (ECOG) Performance Score of 0 or 1 within 14 days prior to enrolment
(vii) Test results within 14 days prior to registration indicate adequate function of vital organs, including bone marrow, liver, and kidney
(viii) Appropriate cardiac function and normal waveforms on a 12-lead electrocardiogram

**Table 3 TAB3:** Exclusion criteria.

Exclusion criteria
(i) Patients for whom auranofin is contraindicated
(ii) Patients who have taken auranofin within 4 weeks prior to obtaining consent
(iii) Patients who have taken anticancer drugs or molecular-targeted drugs within 4 weeks prior to obtaining informed consent
(iv) Patients who are deemed ineligible for enrolment in the clinical study based on the principal investigator (sub-investigator) believing that participation in the clinical study or administration of the test drug will increase their risk
(v) Patients for whom MRI and CT are not suitable
(vi) Patients with difficulty taking oral medications
(vii) Patients otherwise deemed inappropriate for the clinical study by the principal investigator or co-investigator

Study discontinuation criteria

This study will be discontinued for patients who meet one of the conditions listed in Table 4.

**Table 4 TAB4:** Criteria for study discontinuation.

Study discontinuation criteria
(i) If the patient wishes to discontinue
(ii) If a safety issue such as a serious illness occurs
(iii) If adverse events of Common Terminology Criteria for Adverse Events (CTCAE) Grade 3 or higher occur, treatment will be suspended. If the event improves within 6 weeks, treatment will be resumed. If the event does not improve within 6 weeks, treatment will not be resumed
(iv) If efficacy issues such as no improvement in the target disease arise
(v) If a serious event occurs that requires surgical intervention
(vi) If the patient becomes pregnant
(vii) If the patient does not come to the hospital due to relocation or other reasons
(viii) Any other circumstances that require the suspension or interruption of a part or the whole of a clinical study occur

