## Results

Registration

Once inclusion and exclusion criteria would be confirmed and written informed consent would been obtained, patients will be registered through the RedCap system by their treating physician.

Treatment procedure and evaluation

Auranofin 3 mg tablets will be administered orally twice daily after breakfast and dinner for 52 weeks until disease progression, death, or intolerable side effects are observed or until the patient wishes to discontinue the clinical study for other reasons. This dose is equivalent to that used in preclinical in vivo studies. The outcome measures, clinical tests, and evaluation schedule are presented in Table 5.

**Table 5 TAB5:** Schedule of the outcome measures, clinical tests, and evaluation. IC: informed consent; QOL: quality of life; GODDESS: GounderDTRF Desmoid symptom/Impact Scale; PS: performance status; ECG: electrocardiogram

	Pre-registration	Treatment period								Completion	
		Day 1～Week 12						≥Week 12 (2)			
	≤14 days	Day 1 (1)	Week 4	Week 8 (Day 57)	Week 12 (Day 85)	Week 18 (Day 127)	Week 26 (Day 183)	Week 34 (Day 239)	Week 42 (Day 295)	Week 52 (Day 365)	Cessation
			(Day 29)								
Allowable days	‒	‒	±8 days	±8 days	±8 days	±8 days	±14 days	±8 days	±8 days	±8 days	±28 days
Written IC	●										
Screening											
Case selection	●										
Disease evaluation											
Image	●				●		●			●	●
Pain	●		●	●	●	●	●			●	●
(NRS)											
QOL (EQ-5D, GODDESS)	●		●	●	●	●	●	●	●	●	●
Safety assessment											
PS	●	●	●	●	●	●	●	●	●	●	●
Vital signs	●	●	●	●	●	●	●	●	●	●	●
Adverse events			●	●	●	●	●	●	●	●	●
Clinical laboratory tests											
Biochemical testing	●		●	●	●	●	●	●	●	●	●
Hematological tests	●		●	●	●	●	●	●	●	●	●
Urine tests	●		●	●	●	●	●	●	●	●	●
ECG	●						●			●	●

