Day 1 is the start of treatment. Before administration, the patient’s overall condition and vital signs should be evaluated. Even after the primary endpoint is confirmed at Week 26, treatment will generally continue until Week 52, as this is the treatment period. Disease evaluation will continue until the diagnosis of definite disease progression or for the duration of the 52-week clinical study. Radiological evaluation of pre-enrollment examinations will be allowed within four weeks of starting the study drug administration. T1 and T2-weighted MRI images, including target lesions, will be obtained. If an MRI cannot be taken, contrast CT will be taken. The patient’s survival/death and outcome investigation date will be recorded in the case report form. Biochemical tests will be performed on the specified date to assess total protein, albumin, total bilirubin, aspartate aminotransferase, alanine transaminase, alkaline phosphatase, serum creatinine, blood glucose, electrolytes, lipase, and amylase. Hematological tests will be performed on the specified days to assess red blood cell count, white blood cell count, differential white blood cell count, platelet count, hemoglobin, and hematocrit. Urine tests will be performed on the specified days to assess protein, occult blood, and sediment. During continued administration, all illnesses and serious illnesses will be monitored until recovery, stabilization, loss of follow-up, or death is confirmed.

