## Discussion

Follow-up

After the trial is completed at 52 weeks or discontinued at the patient’s request, routine medical care for DF will be provided.

Sample size estimation and statistics

In a previous report, in a phase III, double-blind, randomized controlled trial of sorafenib, the one-year PFS rate was 89% in the sorafenib group and 46% in the placebo group [11] Additionally, in a phase II, randomized, non-comparative trial of pazopanib and MTX + VBL combination therapy, the primary endpoint of the six-month PFS rate was 83.7% in the pazopanib group and 45.0% in the MTX + VBL group [12]. If an effect similar to that of these drugs is observed, it is considered clinically significant. The number of cases required for auranofin administration was calculated to be 21 while assuming a threshold PFS rate of 40% at six months, an expected PFS rate of 70%, a significance level of 10% on both sides, and a detection power of 80%. Assuming that 10% (two cases) would drop out, the target number of cases is 23.

Statistical methods used will include descriptive statistics, Student’s t-test, and Fisher’s exact test as appropriate. The Kaplan-Meier method will be used to analyze survival curves.

Institutional review board approval and registration of the study

The study protocol was approved by the Nagoya University Certified Review Board (number 2021-0259). The study is registered in the Japan Registry of Clinical Trials (jRCT) as jRCTs041210071 (https://jrct.niph.go.jp/). More details about this study can be found on the jRCT website (https://jrct.niph.go.jp/latest-detail/jRCTs041210071). The study will be conducted in accordance with the Declaration of Helsinki, the Clinical Trials Act, and other current legal regulations in Japan.

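### Table 4(iv) takes patients off study for lack of improvement, which conflicts with treating and imaging to progression and can leave the week-26 PFS status of stable patients unknown

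*Protocol article*

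**What the plan says.** The primary endpoint is PFS at 26 weeks (Endpoints). Table 1 groups stable disease with complete and partial response in the rate it reports. Images are scheduled before registration, at weeks 12, 26 and 52, and at cessation (Table 5).

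Four places govern when a patient stops:

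- **Study discontinuation criteria.** "This study will be discontinued for patients who meet one of the conditions listed in Table 4". Item four of that table reads "iv) If efficacy issues such as no improvement in the target disease arise". Item (iii) of the same table suspends the drug for a grade 3 or higher event and then says "If the event improves within 6 weeks, treatment will be resumed", which concerns treatment and not leaving the study.
- **Treatment procedure and evaluation, dosing.** Auranofin is given "for 52 weeks until disease progression, death, or intolerable side effects are observed or until the patient wishes to discontinue the clinical study". Lack of improvement is not listed.
- **Same section, assessment.** "Disease evaluation will continue until the diagnosis of definite disease progression or for the duration of the 52-week clinical study". Also: "Even after the primary endpoint is confirmed at Week 26, treatment will generally continue until Week 52".
- **Follow-up.** "After the trial is completed at 52 weeks or discontinued at the patient’s request, routine medical care for DF will be provided". Only these two routes out of the trial appear there.

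**The concern.** For a patient with stable disease at week 12 these rules give opposite instructions. Table 4(iv) ends the study for that patient, while the treatment section continues both drug and imaging. Stable disease is not a PFS event, so the patients at issue are, at that moment, successes on the primary endpoint.

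If they leave before week 26, their contribution to the primary endpoint depends on an analysis convention and not on an observation. The trial is single-arm and open-label with 21 evaluable patients planned, so no control group absorbs such an effect and the investigator's judgement can trigger the removal. A later analysis plan can choose a convention but cannot recover images that were never taken.

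**Working it through.** **1. The plan's own figure.** Inputs (Sample size estimation and statistics): threshold 40%, expected 70%, 10% two-sided (5% in the upper tail), 80% power, n = 21, target 23. By the exact binomial with success at 13 or more of 21, P(X ≥ 13 | 21, 0.40) = 0.035 and P(X ≥ 13 | 21, 0.70) = 0.852. Power first reaches 80% at n = 19 (0.818) and falls to 0.772 at n = 20. From n = 21 it stays at or above 80% for every n checked, up to 25. Adding two dropouts gives 23. The sample size reproduces and is not at issue.

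**2. Can item (iv) act before week 26, and does the cessation image help?** The first on-treatment image is at week 12 (Day 85). Week 18, the last visit before week 26, is Day 127 ± 8, so Day 135 at the latest. If the ±28 days for the cessation image run from the stop date, that image falls by Day 135 + 28 = 163. The week-26 window opens on Day 183 − 14 = 169. Removal at any scheduled visit before week 26 therefore leaves the cessation image short of the window.

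**3. How many could be affected?** The documents give no figure for auranofin. In the MTX + VBL series they cite, 18 of 30 (60%) had stable disease. With sorafenib the response rate was 33% and the median time to shrinkage 9.6 months, about 42 weeks (9.6 × 365.25/12/7 = 41.7). These are other drugs, but they suggest that the share of progression-free patients without radiological improvement by week 26 need not be small.

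**4. Effect on the estimate.** Assumptions, none from the documents:

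- Events are recorded at weeks 12 and 26, with equal risk in the two intervals, so S12 = √S.
- A fraction f of patients progression-free at week 12 is removed.
- Removed patients have RR times the later progression risk r of those who stay.

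The true rate fixes r = (1 − √S)/(f·RR + 1 − f). If removals are censored, the Kaplan-Meier limit is √S·(1 − r). If they count as failures, it is (1 − f)·√S·(1 − r).

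Example with S = 0.40, f = 0.3, RR = 2: √S = 0.632, r = 0.368/1.3 = 0.283, censored limit 0.632 × 0.717 = 0.454.

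Censored limit when true PFS is 40%:

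| RR | f = 0.1 | f = 0.3 | f = 0.5 | f = 0.7 |
|---|---|---|---|---|
| 1 | 40.0% | 40.0% | 40.0% | 40.0% |
| 1.5 | 41.1% | 43.0% | 44.6% | 46.0% |
| 2 | 42.1% | 45.4% | 47.7% | 49.6% |
| 3 | 43.9% | 48.7% | 51.6% | 53.6% |

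For RR 1.5 to 3 the bias is thus about +1 to +14 points. At true PFS 70% the same grid runs from 70.7% to 78.0%, about +1 to +8 points.

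**5. Effect on the conclusion.** This used 200,000 simulations with n = 21, declaring success when the lower bound of the two-sided 90% log-log interval exceeds 40%. At true PFS 40% the false-positive rate is 0.035 with no removal. With f = 0.3 it is 0.040 (RR = 1), 0.099 (RR = 2) and 0.157 (RR = 3).

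**6. The opposite convention.** At true PFS 70%, f = 0.3, RR = 2, counting removals as failures gives 0.7 × 0.732 = 51.2%. Power falls from 0.85 to 0.22.

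**7. Imaging to week 26.** If removed patients are still imaged at week 26, the rule of 13 or more of 21 keeps its 0.035 and 0.85 whatever f and RR are.

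**The case against.** A reader might infer that the primary endpoint is inflated. The documents do not support that. Nothing says that patients leaving under item (iv) are censored or excluded; Kaplan-Meier is only named. Censoring rules commonly sit in a full protocol or analysis plan, neither of which is shown, so their absence here is no finding. Inflation needs both censoring at removal and a higher later risk in those removed. The second is plausible but not shown.

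Large effects also depend on who leaves. Suppose true PFS is 40% with a constant hazard, so 65.5% are progression-free at week 12. If half of the later progressors leave and nobody else does, Kaplan-Meier reads about 50%. That sits badly with the premise that item (iv) catches stable disease in general. If 30% of the non-progressors leave too, it reads 45%; if half of both groups leave, it reads 40% and the bias is gone.

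Three further points on the other side are fair. Item (iv) may loosely mean treatment failure, though the text does not say so. A cessation image is planned and can record progression up to that point. The assessment sentence, taken alone, already continues imaging regardless of drug. The study is also described as exploratory.

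These points remove the claim of a known direction. They do not remove the contradiction, because Table 4 ends the study itself for the patient and no text requires a week-26 image afterwards.

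**Conclusion.** The concern holds as a conflict between passages that can leave the primary endpoint unobserved in progression-free patients. The size and sign of the bias are not determined by the documents. Under the assumptions above it is about +1 to +14 points at true PFS 40% if removals are censored and carry 1.5 to 3 times the later risk. It is zero if their risk equals that of the others, and negative if they are counted as failures. It would also be zero if they were imaged to week 26. The fractions removed and the risk ratios are assumed, not taken from the trial.

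Counting every lack-of-efficacy removal as a failure in the primary analysis may look like the safe choice. It is not, because it turns patients with stable disease into failures on an endpoint for which stable disease is a success.

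**What to change.** - Reconcile Table 4 with Treatment procedure and evaluation and with Follow-up. Which stopping rule is right is for the clinicians.
- Separate stopping treatment from withdrawing from the study, and place the suspend-and-resume rule in item (iii) under treatment.
- Keep the scheduled week-12 and week-26 images for everyone who stops the drug without progression and has not withdrawn consent.
- Analyse all treated patients by observed progression status at week 26. Where a removed patient has no week-26 image, report sensitivity analyses with such patients censored and with them counted as failures. If removed patients are at no lower risk than the rest, the true rate lies between the two in expectation.

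The cost is a clarification of the text and a few already scheduled images taken off drug. The PFS estimate may be somewhat lower than if these patients were censored.

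### Table 4 (iv) ends the study for lack of improvement, which read literally includes stable disease, while the treatment and evaluation rules run to progression or Week 52 and the primary endpoint does not count a stable tumour as an event

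*Protocol article*

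**What the plan says.** The rules sit in two places in the protocol article.

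- **Materials and methods, Study discontinuation criteria.** The lead-in is mandatory: "This study will be discontinued for patients who meet one of the conditions listed in Table 4". Item (iv) of the table reads "If efficacy issues such as no improvement in the target disease arise". It gives no time point, response category or decision-maker. No item in Table 4 names progression.
- **Results, Treatment procedure and evaluation.** Auranofin is given "for 52 weeks until disease progression, death, or intolerable side effects are observed or until the patient wishes to discontinue the clinical study". Lack of improvement is not in that list. The text below Table 5 adds: "Even after the primary endpoint is confirmed at Week 26, treatment will generally continue until Week 52, as this is the treatment period". On assessment it says: "Disease evaluation will continue until the diagnosis of definite disease progression or for the duration of the 52-week clinical study".

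Table 5 schedules images before registration, at Weeks 12, 26 and 52, and at cessation (±28 days). The primary endpoint is PFS at 26 weeks, and Table 1 lists stable disease beside complete and partial response.

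**The concern.** A patient whose tumour is unchanged at the Week 12 image has not progressed, so the treatment section keeps that patient on drug and under evaluation, and the primary endpoint can count the patient as a success at Week 26. The same patient has not improved in the plain sense of the word, so Table 4 (iv) ends the study for that patient. Both rules cannot be followed, and the article does not say which prevails.

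Stable disease is not a rare state in the article's own background evidence. The Introduction reports stable disease in 18 of 30 patients (60%) on methotrexate plus vinblastine. For sorafenib it says "the response rate was 33%, and the median time to tumor shrinkage and evaluation was 9.6 months". If Table 4 is followed to the letter, patients whom the primary endpoint would count as successes may have no Week 26 image. With 21 evaluable patients planned, a few such losses matter.

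**Working it through.** **1. Can the outcome actually be lost?** Table 5 places Week 12 at Day 85 ± 8 and Week 26 at Day 183 ± 14. Suppose a patient is stopped on the day of the Week 12 image. The cessation image then falls no later than Day 85 + 8 + 28 = 121. The Week 26 window opens on Day 183 − 14 = 169. The cessation image therefore cannot show Week 26 status, and Table 5 schedules no image after cessation. Only the general evaluation rule below Table 5 could keep the Week 26 image, and it does not say whether it covers patients stopped under Table 4.

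**2. The planned sample size.** Inputs from Discussion, Sample size estimation and statistics: threshold 0.40, expected 0.70, two-sided 10% (5% in the upper tail), power 80%. The article names no test for the primary endpoint, so an exact binomial test is assumed here.

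- n = 19, success at 12 or more: power 0.818.
- n = 20, success at 13 or more: power 0.772.
- n = 21, success at 13 or more: P(X ≥ 13 | 0.40) = 0.035 and P(X ≥ 13 | 0.70) = 0.852.

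From n = 21 upward (checked to 29), power stays at or above 80%, so the stated 21 is reproduced. Adding two dropouts gives the target of 23. The sample size is not in dispute.

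**3. Stopped patients counted as failures.** Let f be the share of would-be successes stopped under (iv). The article gives no f, so the values are assumptions. The success rate becomes 0.70 × (1 − f), and power is P(X ≥ 13) with n = 21.

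| f | success rate | expected successes of 21 | power |
|---|---|---|---|
| 0 | 0.70 | 14.7 | 0.852 |
| 10% | 0.63 | 13.2 | 0.636 |
| 20% | 0.56 | 11.8 | 0.376 |
| 30% | 0.49 | 10.3 | 0.167 |

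With all 23 patients and success at 14 or more, power is 0.880, 0.671, 0.401 and 0.176.

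**4. Stopped patients censored, or dropped.** This needs a model, and every input except the 0.40 threshold is assumed. A share m of patients improve and do not progress by Week 26. The others progress at a constant rate that makes overall PFS at 26 weeks 0.40:

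- s26 = (0.40 − m)/(1 − m), and s12 = s26^(12/26).
- Half of the non-improvers still progression-free at Week 12 are stopped: c = (1 − m) × s12 / 2.
- Observed successes: k = m + (0.40 − m)/2.
- Kaplan-Meier with censoring at Week 12: [m + (1 − m) × s12] × k/(m + c).
- Dropped from the denominator: k/(1 − c).

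| m | s12 | c | k | censored | dropped |
|---|---|---|---|---|---|
| 0.1 | 0.602 | 0.271 | 0.25 | 0.433 | 0.343 |
| 0.2 | 0.527 | 0.211 | 0.30 | 0.454 | 0.380 |
| 0.3 | 0.407 | 0.143 | 0.35 | 0.463 | 0.408 |

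The true value is 0.40 in every row. Censoring pushes the estimate up. Dropping pushes it down in two rows and leaves it almost unchanged in the third.

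**The case against.** The best defence is that item (iv) is loose wording for treatment failure. Table 4 has no other item where progression could sit, although the treatment section stops for it. On that reading stable patients are untouched. This is plausible and lowers confidence, but the written words are wider than progression, and the treatment section uses the word progression when it means it.

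A second defence is that evaluation continues to definite progression or through the 52 weeks with no stated exception, and that an image is due at cessation. This stands in part: loss of the Week 26 outcome is possible, not certain. Against it, Table 4 discontinues the study and not only the drug, and a cessation image soon after Week 12 comes too early.

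A third is that how stopped patients are counted normally belongs in the full protocol or analysis plan, which are not shown. That is accepted. The fault is the conflict between rules, not a missing analysis rule.

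A reader might also infer more than the text supports:

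- *That nearly all patients would meet (iv).* Applying the sorafenib response figures to Week 12 or Week 26 suggests this, but only if improvement means tumour response. Table 4 does not say so. The study also measures pain, quality of life and T2 signal. Entry requires recent progression, or inoperable disease with worsening function, so halted growth might itself be called improvement.
- *That investigators choose whom to stop.* Table 4 names no decision-maker. An undefined criterion in an open-label study leaves room for judgement, but that is inference.
- *That censoring and dropping both inflate PFS.* The table above shows that dropping does not.
- *That the false-positive rate can be read off by putting the inflated Kaplan-Meier value into the binomial tail.* That treats all 21 patients as fully observed when the model censors 14% to 27% of them at Week 12, so it is not a valid test size.

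**Conclusion.** The conflict is in the current text and bears on the primary endpoint. Followed literally, Table 4 (iv) can remove before Week 26 patients whom the endpoint would count as successes. The article fixes neither how many would be stopped nor how they would count, so no single size can be given. Under the assumed exact test, counting 10% to 30% of would-be successes as failures lowers power from 85% to between 64% and 17%. In the two-group model at a true PFS of 0.40, censoring gives 0.43 to 0.46 and dropping gives 0.34 to 0.41. These figures show sensitivity and do not predict the result. Confidence is moderate, because item (iv) may have been meant as progression and the evaluation rule may already protect the Week 26 image.

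**What to change.** Reconcile Table 4 (iv) with the treatment and evaluation text so that one efficacy-based stopping criterion applies throughout. Which criterion is a clinical decision for the investigator.

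Whichever is chosen, state that the rule continuing disease evaluation to definite progression or through the 52 weeks also covers patients stopped under (iv) without documented progression. They then keep the scheduled Week 26 image and are classified from it in the primary analysis. Report how many patients were stopped under (iv).

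The cost is a wording change in Table 4 and a sentence or two elsewhere. No patients are added, and the Week 26 image is already in the schedule. The small downside is that patients stopped early must still attend for that scan.
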